**3.12 Proposed outcome measures:**

The primary outcome will be OCD symptoms as measured by the Yale Brown Obsessive Compulsive Checklist YBOCS [12] observer-report version. Secondary outcomes will include self-reported health-related quality of life (SF-36), self-reported OCD symptoms (YBOCs self-rated), generic mental health (CORE-OM), depression (PHQ9), anxiety (GAD-7), functioning (WSA), health-related quality of life (EQ5D), employment status (IAPT Employment Status questions A13 –A15), patient satisfaction (CSQ) and acceptability (qualitative interviews), and % patients not improved or partially improved requiring more intensive CBT. Our primary outcome point (3 month follow up) will be determined by the pilot study. A 6 and 12 month follow up will also be included.

**4. Research Governance:**

*Trial sponsorship:* The University of Manchester has agreed to act as sponsor.

*Trial management:* The trial management group will meet quarterly and will include the principal investigator, all other investigators, and trial manager to discuss the progression and day to day management issues of the trial. The principal investigator will be responsible for the overall leadership, management and outputs of the study. The principal investigator will maintain a log of the key milestones to be achieved against the timetable (as outlined in the section below). Progress of these milestones and corresponding timetable will be reported at the quarterly meetings to ensure progression of the trial and to agree corrective action if necessary. The trial manager (based in Manchester) will be responsible for the day to day running and coordination of the study and will be accountable to the principal investigator. Their role will include obtaining ethics and research governance approval, coordinating the collection of data, preparation of meetings and assisting with the writing and execution of the procedures and policies for the trial, producing initial drafts for research papers and disseminating the study’s findings. They will also be responsible for ensuring recruitment is on target by collating monthly reports from each site researcher and reporting this to the PI, such a monitoring system will allow for corrective action to be taken at the earliest opportunity. Site research workers supervised by the site lead will be responsible for recruitment, the conduct of eligibility and follow up assessments and data collection. They will also be responsible for conducting qualitative acceptability interviews at post treatment. Data will be securely stored locally and entered on a secure electronic recording system. Data will be checked by the trial manager for errors and data completion prior to transfer to the trial statistician. The trial statistician will be responsible for cleaning the data, conducting the analysis and sending the data to the DMEC. We are using the services of the York Trials Unit who will provide a secure allocation of trial participants to treatment and will be responsible for the minimisation process. They will also provide a comprehensive data management service including devising the electronically secure recording system.

*Trial Steering Committee:* A trial steering committee (TSC) will be established and comprise of an independent chair who has expertise in both trials and OCD and two other independent members including a user representative who has had lived experience with OCD and a clinician working with people with OCD.

*Data Monitoring and Ethics Committee (DMEC):* A DMEC will be established to assess the progress and safety of the study. It will consist of members external to the study team including a statistician, a clinician and an expert in health services trials. A DMEC report template will be devised for reporting purposes and agreed by the DMEC committee prior to the commencement of the study.

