To reduce detection bias, we will aim to blind researchers undertaking outcome assessments to participants’ treatment allocation. To facilitate blinding, we will use the following procedures: 1) ensuring that the outcome assessments conducted by research workers are completed on different days or locations from the clinical areas in which treatment is being conducted; and 2) asking participants to refrain from revealing their treatment allocation at follow-up assessments. Finally we will test blinding by asking research workers to guess the treatment allocation of the patient at each follow-up and to record the number of patients who inadvertently reveal their treatment allocation.

***Concurrent Process Evaluation:*** Criticism has been aimed at RCTs which only focus on pre-specified health outcomes [14]. Process evaluation within trials is recommended to examine key issues such as implementation, acceptability and feasibility which add to the understanding of the RCT results. This study will conduct a process evaluation to explore the barriers and facilitators of implementation by examining the extent to which: i) patients comply with treatment and ii) patients and health professionals find treatment acceptable.

***i) The extent to which patients comply with treatment***: A key aspect of any treatment is the extent to which users complete their agreed course of treatment including CBT between-session tasks. Treatment compliance will be examined through recording the number of sessions attended, and use of self-help materials. With cCBT we will collect automated recordings of the frequency and duration of cCBT use, and patient self reports of time spent between sessions doing CBT based tasks. In the bibliotherapy arm we will collect number, duration and mode of contact (telephone or face to face) via mental health worker records as well as patient diaries of between session work.

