***i) The extent to which patients and health professionals find interventions acceptable:*** Successful implementation of research into NHS practise requires that new interventions are accepted and welcomed by both patients and mental health professionals. The 8-item Client Satisfaction Questionnaire (CSQ) will be administered to all patients at 3 and 6 months to assess acceptability. Qualitative interviews will be conducted at post-intervention with a subgroup of 10% of patients stratified by baseline severity in both active intervention arms of the trial across clinical sites. Patients will be sampled on characteristics including gender, ethnicity & outcome. We expect to conduct approximately 40-48 interviews (11-12 interviews at each site). We will also conduct exit interviews with participants who leave treatment early. A sample of 15-20 health professionals will be interviewed with the aim of exploring potential barriers and facilitators to implementing GSH and cCBT into clinical practice. Participants will be identified from health professionals who are working in our sites, and will include those who are delivering treatments in the trial, and those who work in our sites but are not treating patients as part of our trial, to maximise variation. The CSQ will be used to compare patient satisfaction across the treatment arms and, with other quantitative data, to identify predictors of satisfaction. Interviews will be conducted face-to-face, by telephone or by Skype dependent on participant preference and feasibility. Acceptability and exit interviews will be transcribed verbatim and data will be analysed using a framework analysis. An initial coding framework will be developed and transcripts checked against the framework to ensure that there are no significant omissions. Codes in each interview will be examined across individual transcripts as well as across the entire data set and allocated to the framework. Using aspects of the constant comparative method of analysis broader categories using linking codes will be developed across interviews. Data will be interpreted and analysed within the framework to structure patients’ views about each intervention and reasons for leaving the intervention early.

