**3.10 Statistical analysis:**

A full statistical analysis plan for the analysis of primary and secondary outcome measures including any sub-group analyses will be prepared and presented to the TSC (Trial Steering Committee) prior to the commencement of the trial analysis. During the recruitment and follow-up period regular reports will be prepared for the TSC/DMEC on data quality.

Statistical analysis of outcome will follow intention-to-treat principles: patients will be analysed according to randomised group and outcome data will be sought and included in the analysis for all patients irrespective of completion of treatment. Preliminary statistical analysis will model the pattern of missing data in terms of baseline characteristics of patients.

Statistical analyses of the primary outcome measure, YBOC at 3 months, will be based on a mixed model analysis with random effects for therapist and covariates including baseline YBOC and variables potentially predictive of outcome including minimisation variables. This will be used to compare all three arms. Conditional on significance at a 5% level, pairwise comparisons between arms will be carried out using a Bonferroni corrected p-value. Similar analyses will be carried out for quantitative secondary outcomes. A logistic mixed model will be use to compare the percentage of patients requiring full CBT between treatment adjusted for baseline severity.

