**8. Justification of support required:**

Each of the four sites will require a research worker (grade 6) WTE for the first 3 years of the trial and reducing to 0.4 for the final year to facilitate recruitment, conduct eligibility and follow up assessments. Site researchers will also be responsible for conducting qualitative acceptability interviews at post treatment. [name] will lead the economic analysis supported by a research worker for 0.25 WTE. A 0.8 WTE trial manager will be based at the University of Manchester and will be responsible for the day to day running and coordination of the trial. A 0.1 WTE trial manager will be based in the York Clinical Trials Unit to co ordinate and supervise data management and to interface with the rest of the trial sites. In addition to staff costs above we will need funding to purchase sufficient internet delivered OCD treatment packages (OCfighter) for all the people taking part in the study, costs for York clinical trials unit for randomisation, data entry, and cleaning and preparation of data for analysis. We will also need funds for travel expenses of the trial team and assessment visits, and costs associated with project administration (e.g. postage and office supplies). NHS sites in each of the geographical areas taking part in our study will need money towards their administrative costs, training time, supervision, utilities, and workspace and overhead charges during the time that we are working in or at their buildings.

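### No rule separates the acceptability interviewer from the blinded YBOCS rater, so the later ratings of interviewed active-arm patients can be unblinded

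*Protocol*

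**What the plan says.** **Outcome.** Section 3.12 states: "The primary outcome will be OCD symptoms as measured by the Yale Brown Obsessive Compulsive Checklist YBOCS [12] observer-report version". Section 3.10 sets the primary time point: "Statistical analyses of the primary outcome measure, YBOC at 3 months". Ratings are also planned at 6 and 12 months.

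**Blinding aim.** In section 3.3.2, "we will aim to blind researchers undertaking outcome assessments". The measures are to hold assessments apart, in time or place, from treatment; to ask participants not to disclose their arm; and to check success by having assessors guess the arm and log disclosures.

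**Who rates.** Section 4: "Site research workers supervised by the site lead will be responsible for recruitment, the conduct of eligibility and follow up assessments and data collection".

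**Who interviews.** The next statement of duties in section 4 is "They will also be responsible for conducting qualitative acceptability interviews at post treatment". Section 8 says the same: "Site researchers will also be responsible for conducting qualitative acceptability interviews at post treatment".

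**How many staff.** Section 8: "Each of the four sites will require a research worker (grade 6) WTE for the first 3 years of the trial".

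**Who is interviewed.** The process-evaluation part of section 3.3.2 draws 10% of patients from both active arms, expects about 40 to 48 interviews, and explores views of each intervention. It lists outcome among the sampling characteristics and allows face-to-face, telephone or Skype contact. It adds: "We will also conduct exit interviews with participants who leave treatment early". No interviewer or timing is given for these exit interviews.

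**The concern.** Patients in this trial know their arm, so blinded rating is the main protection against detection bias on the observer-rated scale. An acceptability interview removes it for the patient concerned. Being selected shows that the patient is not on the waiting list, and the conversation shows which package was used. Separating assessments from the clinic and asking patients not to disclose do not help when the assessor's own duties include asking about the treatment. The guess-and-log check would record the loss of blinding without preventing it.

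The exposure falls on one side of each comparison with the waiting list, so randomisation does not balance it and a larger sample does not shrink it. Section 3.11 shows that the protocol recognises this kind of risk: data on intervention resources come from therapist records partly so that assessors stay blind. The interviews have no matching protection.

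**Working it through.** The protocol gives no figure to reproduce on this point. The check traces the roles and then sizes the exposure.

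**Roles**

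1. Sections 4 and 8 give the follow-up assessments and the acceptability interviews to the same staff group.
2. Section 8 funds one such post per site, so at a given site the natural reading is that one person does both.
3. Section 3.3.2 takes the patient interviews from the active arms only.
4. No section names a separate interviewer, a swap between sites, or a rule on the order of interview and rating.

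**Which ratings are exposed**

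- *6 and 12 months.* These follow a post-treatment interview. They are unblinded whenever the interviewer is also the rater.
- *3 months (primary).* Treatment lasts 12 weeks, so the post-treatment interview and the 3-month rating fall at about the same time and their order is not fixed. Sampling on outcome suggests that the rating comes first but does not require it. Exit interviews with early leavers could precede the 3-month rating.

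**Share of patients**

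Inputs: 432 patients (section 3.8); three arms, assumed equal; interviews assumed to be spread evenly over the two active arms.

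- Active-arm patients: 432 × 2/3 = 288.
- If the stated percentage governs: 10% × 288 = 28.8, about 29 patients.
- If the stated count governs: 40/288 = 13.9% to 48/288 = 16.7%.
- Waiting list: 0% by design.

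The percentage and the count do not agree. The count is closer to 10% of the whole trial (10% × 432 = 43.2) than to 10% of the active arms. Both are carried forward, giving 10% to 17%. Exit interviews would add to this, but their number is not given.

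**Possible effect on a contrast**

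Shift in the contrast of one active arm with the waiting list = share interviewed × mean rater shift in interviewed patients. The rater shift is an assumption; the documents give none.

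| Assumed rater shift (YBOCS points) | Share 10% | Share 13.9% | Share 16.7% |
| --- | --- | --- | --- |
| 1 | 0.10 | 0.14 | 0.17 |
| 2 | 0.20 | 0.28 | 0.33 |
| 3 | 0.30 | 0.42 | 0.50 |

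If only 85% of the active arms are followed up (288 × 0.85 = 244.8) and every interviewed patient is retained, the largest entry becomes 3 × 48/244.8 = 0.59. For scale, the difference targeted in section 3.8 is 3 points.

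For cCBT against bibliotherapy both arms are interviewed, so similar shares and shifts largely cancel and no clear bias follows.

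**The case against.** The strongest reply is that the primary endpoint is mostly untouched. Outcome is one of the sampling characteristics, which fits interviews held after the 3-month rating, and 6 and 12 months are secondary time points by which all arms may have had conventional CBT. This stands, and it limits the point. A reader might infer that the plan unblinds its own primary assessment by design. The documents do not support that: no text places an acceptability interview before the 3-month rating, and sections 4 and 8 do not assign the exit interviews to site researchers.

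Second, the text does not require that a patient's interviewer be that patient's rater. There are four site posts, interviews may be remote, section 7 lets service users take a proportion if they wish, and section 5 refers to research assistants at each site in the plural. This also stands in part: the protocol permits separation. But it assigns both duties to the same post and makes nothing that would separate them compulsory.

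Third, the existing safeguards still work for the 83% to 90% of active-arm patients not sampled for interview, for the waiting list, and for any rating made before an interview. That is correct. The option of postal or telephone follow-up, by contrast, does not change who makes the observer rating.

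**Conclusion.** The point holds as a missing separation rule. Followed as written, with one worker per site doing both jobs, the plan defeats its blinding aim at 6 and 12 months for about 10% to 17% of active-arm patients and for none of the waiting list. This rests on equal allocation and on the reading of one researcher per site. At 3 months the exposure is conditional on an interview coming first and cannot be sized from the documents.

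The 0.1 to 0.5 point range applies to 6 and 12 months and depends wholly on an assumed rater shift. It should not be read as a bias in the primary result. The direction is not established either, since it depends on what the raters expect.

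This is an inexpensive correction worth making, not a flaw that invalidates the primary comparison. It is best made before interviews begin, because a rating made by an unblinded assessor cannot be repaired afterwards.

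**What to change.** Amend the process-evaluation text in section 3.3.2 and the staff duties in sections 4 and 8 to state that:

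1. A patient's acceptability or exit interview is done by someone with no YBOCS ratings still to make for that patient. This can be another site's research worker by telephone or Skype, or a service-user interviewer trained as section 7 foresees.
2. If the patient's own rater has to do the interview, it takes place only after the 3-month YBOCS, and a researcher from a different site makes that patient's later ratings.
3. The interviewer for exit interviews is named and their timing relative to the 3-month rating is fixed.

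The same amendment should settle whether the patient sample is 10% of the active arms (about 29) or 40 to 48.

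**Cost.** Protocol wording and cross-site scheduling of roughly 30 to 50 interviews plus the exit interviews, with no additional post. Some exit interviews would be held later or with an interviewer whom the patient does not know.

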**5. Project timetable and milestones:**

| **Date** | **Milestones** |
| --- | --- |
| Months 1-3 | Apply for ethics and governance approval for all sites  Apply for adoption by MHRN  Advertise and appoint trial manager and Research Assistants at each site  Develop procedures and policies for the conduct of the trial  Conduct training in GSH and cCBT and develop training manuals  Initial adaptation of AD-SUS  Appoint members to the trial steering committee and DMEC |
| Months 4-13 | Recruitment to pilot study (n=153; Estimated recruitment rate=17/mth)  Pilot testing of AD-SUS  Delivery of interventions  Report to DMEC, TSC and interim report to HTA regarding continued funding. |
| Months 14 -43 | Proceed to full trial after agreement from HTA  Recruitment and intervention (months 14-31; (n 279; Estimated recruitment rate=17/mth)  Data collection at 3, 6 and 12 month follow-up (Final follow up month 43)  Conduct and analyse acceptability interviews |
| Months 43-48 | Closing of database  Data cleaning, statistical & economic analysis  Prepare final report for HTA  Send trial participants details of study findings  International conference to present main findings  Final report disseminated as a publication, user websites and a conference for dissemination of final results. |

**7. Service users:**

Service user input, involvement and dissemination of the proposed study comes from [name] (applicant) Chief Executive of Anxiety UK. We have strong links with Anxiety UK and currently have a number of funded (including both a NIHR programme grant and an HTA grant) and unfunded collaborative studies (a qualitative study of CBT telephone acceptability for anxiety and depression, applicants [name], [name] & [name]). In addition we will also invite members of a CCBT OCD sub group of the Patient and Public Involvement in Research Group in Norfolk who have agreed to be part of our steering committee. Our service user representation will also include assisting us in developing the interview schedules for the acceptability interviews. We will also offer service users training in interviewing if they wish to conduct a proportion of the interviews and they will contribute to the analysis of the interviews and assist in the writing of publications. We are strongly committed to user involvement in our research endeavours and applicants ([name], [name]) have conducted a workshop under the auspices of the Institute of Health Sciences of engaging meaningful user involvement in research. A proportion of [name] time will be funded through the grant. A consultancy fee will be paid to participating members of the patient and public involvement in research group.

**8. Justification of support required:**

Each of the four sites will require a research worker (grade 6) WTE for the first 3 years of the trial and reducing to 0.4 for the final year to facilitate recruitment, conduct eligibility and follow up assessments. Site researchers will also be responsible for conducting qualitative acceptability interviews at post treatment. [name] will lead the economic analysis supported by a research worker for 0.25 WTE. A 0.8 WTE trial manager will be based at the University of Manchester and will be responsible for the day to day running and coordination of the trial. A 0.1 WTE trial manager will be based in the York Clinical Trials Unit to co ordinate and supervise data management and to interface with the rest of the trial sites. In addition to staff costs above we will need funding to purchase sufficient internet delivered OCD treatment packages (OCfighter) for all the people taking part in the study, costs for York clinical trials unit for randomisation, data entry, and cleaning and preparation of data for analysis. We will also need funds for travel expenses of the trial team and assessment visits, and costs associated with project administration (e.g. postage and office supplies). NHS sites in each of the geographical areas taking part in our study will need money towards their administrative costs, training time, supervision, utilities, and workspace and overhead charges during the time that we are working in or at their buildings.

